**Reporting procedures for all adverse events**

All AEs and SAEs occurring within the 28 and 184 days following injection and observed by the Investigator or reported by the volunteer, respectively, whether or not attributed to study intervention, will be recorded in the CRF. The investigator will assess every AE for seriousness and causality. A second assessment will be performed by a separate person (the Sponsor or delegate). All AEs that result in a volunteer's withdrawal from the study will be followed up until a satisfactory resolution occurs, or until a non-study related causality is assigned (if the volunteer consents to this).

**Reporting procedures for SAE**

Following the occurrence of any SAE, the trial subject's randomization code may be broken (see Section 6.4) and the PI shall report the event to the local safety monitor, the DSMB, the Sponsor, the vaccine manufacturer within 24 hours. In the case of a SAE considered possibly, probably or definitely related to the study medication, the PI will notify the other 3 PIs in the Consortium and WHO within 24 hours. For non-fatal SAE, the PI shall also report the event to the National EC and WHO EC, by means of the annual report. For SAE resulting in death, the PI shall report the event to the National EC as soon as possible but not later than 7 calendar days. WHO will report the event to its EC as soon as possible but not later than 7 calendar days.

**Reporting procedures for SUSAR**

Following the occurrence of a SUSAR, the trial subject's randomization code shall be broken (see Section 6.4) and the PI shall report the event to the local safety monitor, the DSMB, the Sponsor, the vaccine manufacturer, the other 3 PIs in the consortium and WHO within 24 hours. The PI shall also report the event to the National EC as soon as possible but not later than 7 calendar days for SUSAR resulting in death and 15 calendar days for non-fatal SUSAR. WHO will report the event to its EC as soon as possible but not later than 7 calendar days.

Of note, given that this first-in-human trial tests a GMO, the SAE will be assessed not only with regard to the GMO itself but also to the following aspects:

- Suspected viral or bacterial contamination from the GMO during initial preparation or later reconditioning
- A potential quality defect in the GMO or its components (medium, vector, etc.)
- A previously undetected disruption of the cold chain
- The administration (injection) of the GMO

### Assessment of severity

The severity of clinical and laboratory AE will be assessed according to the scales in Tables 3 - 5.

Toxicity grading scale for local adverse events.

| Toxicity grading scale for local adverse events |         |                                               |                                     |                         |                                         |
|-------------------------------------------------|---------|-----------------------------------------------|-------------------------------------|-------------------------|-----------------------------------------|
| Local Reaction                                  | Grade 0 | Grade 1                                       | Grade 2                             | Grade 3                 | Grade 4                                 |
|                                                 | Normal  | Mild                                          | Moderate                            | Severe                  | Potentially life-threatening            |
| Redness/erythema*                               | < 25 mm | 25-50 mm                                      | 51-100 mm                           | > 100 mm                | Necrosis or exfoliative dermatitis      |
| Swelling/induration**                           | < 25 mm | 25-50 mm and does not interfere with activity | > 50 mm or interferes with activity | prevents daily activity | Necrosis                                |
| Pain                                            | None    | Does not interfere with activity              | Interferes with activity            | Prevents daily activity | Emergency room visit or hospitalization |

\*In addition to grading the measured local reaction at the greatest single diameter, the measurement should be recorded as a continuous variable.

\*\*Induration/swelling should be evaluated and graded using the functional scale as well as the actual measurement.

From the FDA's 2007 voluntary guidance:

(<http://www.fda.gov/downloads/BiologicsBloodVaccines/GuidanceComplianceRegulatoryInformation/Guidances/Vaccines/ucm091977.pdf>)

Table 4: Toxicity grading scale for physical observations.

| Physical observations |                                          |                                                        |                                                                      |                                                              |         |
|-----------------------|------------------------------------------|--------------------------------------------------------|----------------------------------------------------------------------|--------------------------------------------------------------|---------|
| Observation           | Grade 1                                  | Grade 2                                                | Grade 3                                                              | Grade 4                                                      | Grade 5 |
| Fever (axillary)      | 38.0° - 39.0°C                           | > 39.0°C - 40.0°C                                      | > 40.0°C for ≤ 24 hours                                              | > 40.0°C for ≥ 24 hours                                      | Death   |
| Tachycardia (bpm)*    | Asymptomatic, intervention not indicated | Symptomatic, non-urgent medical intervention indicated | Urgent medical intervention indicated                                | Life-threatening consequences, urgent intervention indicated | Death   |
| Bradycardia (bpm)**   | Asymptomatic, intervention not indicated | Symptomatic, medical intervention indicated            | Severe, medically significant, urgent medical intervention indicated | Life-threatening consequences, urgent intervention indicated | Death   |

| Physical observations |                                                                             |                                                                                                                                                                                                                                                                            |                                                                                                                                                                                                   |                                                                                                                                                             |         |
|-----------------------|-----------------------------------------------------------------------------|----------------------------------------------------------------------------------------------------------------------------------------------------------------------------------------------------------------------------------------------------------------------------|---------------------------------------------------------------------------------------------------------------------------------------------------------------------------------------------------|-------------------------------------------------------------------------------------------------------------------------------------------------------------|---------|
| Observation           | Grade 1                                                                     | Grade 2                                                                                                                                                                                                                                                                    | Grade 3                                                                                                                                                                                           | Grade 4                                                                                                                                                     | Grade 5 |
| Hypertension**        | Prehypertension (systolic BP 120 - 139 mm Hg or diastolic BP 80 - 89 mm Hg) | Stage 1 hypertension (systolic BP 140 - 159 mm Hg or diastolic BP 90 - 99 mm Hg); medical intervention indicated; recurrent or persistent ( $\geq 24$ h); symptomatic increase by $> 20$ mm Hg (diastolic) or to $> 140/90$ mm Hg if previously WNL; monotherapy indicated | Stage 2 hypertension (systolic BP $\geq 160$ mm Hg or diastolic BP $\geq 100$ mm Hg); medical intervention indicated; more than one drug or more intensive therapy than previously used indicated | Life-threatening consequences (e.g., malignant hypertension, transient or permanent neurologic deficit, hypertensive crisis); urgent intervention indicated | Death   |
| Hypotension           | Asymptomatic, intervention not indicated                                    | Non-urgent medical intervention indicated                                                                                                                                                                                                                                  | Medical intervention or hospitalization indicated                                                                                                                                                 | Life-threatening and urgent intervention indicated                                                                                                          | Death   |

| Definitions  |                                                                                                                                                  |
|--------------|--------------------------------------------------------------------------------------------------------------------------------------------------|
| Fever        | A disorder characterized by elevation of the body's temperature above the upper limit of normal.                                                 |
| Tachycardia  | A disorder characterized by a dysrhythmia with a heart rate greater than 100 beats per minute.                                                   |
| Bradycardia  | A disorder characterized by a dysrhythmia with a heart rate less than 60 beats per minute.                                                       |
| Hypertension | A disorder characterized by a pathological increase in blood pressure; a repeatedly elevation in the blood pressure exceeding 140 over 90 mm Hg. |
| Hypotension  | A disorder characterized by a blood pressure that is below the normal expected for an individual in a given environment.                         |

\*Taken after  $\geq 10$  minutes at rest; \*\*when resting heart rate is between 60 – 100 beats per minute. Use clinical judgment when characterizing bradycardia among some healthy subjects, for example, conditioned athletes.

From CTCAE v4 ([http://evs.nci.nih.gov/ftp1/CTCAE/CTCAE\\_4.03\\_2010-06-14\\_QuickReference\\_5x7.pdf](http://evs.nci.nih.gov/ftp1/CTCAE/CTCAE_4.03_2010-06-14_QuickReference_5x7.pdf))

Toxicity grading scale for systemic AEs excluding the physical observations listed above.

| Toxicity grading scale for systemic adverse events |                               |                                 |                                      |                                             |
|----------------------------------------------------|-------------------------------|---------------------------------|--------------------------------------|---------------------------------------------|
| Systemic sign/symptom                              | Grade 1

Mild           | Grade 2

Moderate         | Grade 3

Severe                | Grade 4

Potentially life-threatening |
| Headache                                           | No interference with activity | Some interference with activity | Significant; prevents daily activity | Medical consultation and/or hospitalization |
| Fatigue                                            | No interference with activity | Some interference with activity | Significant; prevents daily activity | Medical consultation or hospitalization     |
| Myalgia                                            | No interference with activity | Some interference with activity | Significant; prevents daily activity | Medical consultation and/or hospitalization |
| Arthralgia                                         | No interference with activity | Some interference with activity | Significant; prevents daily activity | Medical consultation and/or hospitalization |
| Chills                                             | No interference with activity | Some interference with activity | Significant; prevents daily activity | Medical consultation and/or hospitalization |
| Sweats                                             | No interference with activity | Some interference with activity | Significant; prevents daily activity | Medical consultation and/or hospitalization |

|                         |                               |                                                                    |                                                           |                                             |
|-------------------------|-------------------------------|--------------------------------------------------------------------|-----------------------------------------------------------|---------------------------------------------|
| Subjective Fever        | No interference with activity | Some interference with activity                                    | Significant; prevents daily activity                      | Medical consultation and/or hospitalization |
| Nausea                  | No interference with activity | Some interference with activity not requiring medical intervention | Prevents daily activity and requires medical intervention | Medical consultation and/or hospitalization |
| Vomiting                | No interference with activity | Some interference with activity not requiring medical intervention | Prevents daily activity and requires medical intervention | Medical consultation and/or hospitalization |
| Abdominal Pain          | No interference with activity | Some interference with activity not requiring medical intervention | Prevents daily activity and requires medical intervention | Medical consultation and/or hospitalization |
| Diarrhea                | No interference with activity | Some interference with activity not requiring medical intervention | Prevents daily activity and requires medical intervention | Medical consultation and/or hospitalization |
| Other systemic symptoms | No interference with activity | Some interference with activity                                    | Prevents daily activity                                   | Medical consultation and/or hospitalization |

From the FDA's 2007 voluntary guidance:

(<http://www.fda.gov/downloads/BiologicsBloodVaccines/GuidanceComplianceRegulatoryInformation/Guidances/Vaccines/ucm091977.pdf>)

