| Stopping rules     | 
The study will be placed on safety hold in case of occurrence of a vaccine related SAE
                                                                                                                                                                                                                                                                                                                                                                                                                                                                                                                                                                                                                                                                                                                                                                                                                                                                                                                                                                                                                                                                                                                                                        |
| Sample Size        | 
– A total of 201 volunteers will be enrolled in this trial
 
 
• 20 Volunteers aged between 18 and 50 years inclusive, who will receive <math>3 \times 10^3</math> pfu of VSV<math>\Delta</math>G-ZEBOV vaccine IM
 
• 20 Volunteers aged between 18 and 50 years inclusive, who will receive <math>3 \times 10^4</math> pfu of VSV<math>\Delta</math>G-ZEBOV vaccine IM
 
• 20 Volunteers aged between 18 and 50 years inclusive, who will receive <math>3 \times 10^5</math> pfu of VSV<math>\Delta</math>G-ZEBOV vaccine IM
 
• 39 Volunteers aged between 18 and 50 years inclusive, who will receive <math>3 \times 10^6</math> pfu of VSV<math>\Delta</math>G-ZEBOV vaccine IM
 
• 62 Volunteer aged between 18 and 50 years inclusive, who will receive <math>2 \times 10^7</math> pfu of VSV<math>\Delta</math>G-ZEBOV vaccine IM
 
• 20 Volunteers aged between 13 and 17 years inclusive, who will receive <math>2 \times 10^7</math> pfu of VSV<math>\Delta</math>G-ZEBOV vaccine IM
 
• 20 Volunteers aged between 6 and 12 years inclusive, who will receive <math>2 \times 10^7</math> pfu of VSV<math>\Delta</math>G-ZEBOV vaccine IM.
 
 |

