## **4.2. Objectives**

### **Primary Objectives:**

- To evaluate the safety and tolerability of five different doses of VSVΔG-ZEBOV vaccine in three different age groups.

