### 4.3. Endpoints

#### Primary Endpoints

The nature, frequency, and severity of adverse events (AEs) and/or serious adverse events (SAEs) associated with administration of BPSC1001 at 5 different doses measured as follow:

- Frequency and severity of local injection site reactogenicity signs and symptoms: pain, erythema, and induration until day 14 post vaccination (solicited local symptoms)
- Frequency and severity of systemic reactogenicity signs and symptoms until day 14 post vaccination (solicited general symptoms)
- Frequency of adverse events (AEs), severity and assessed relationship to study products until day 28 post vaccination (unsolicited AE)
- Detailed description of all serious adverse events (SAEs) until day 28 post vaccination
- Distribution of values of safety laboratory measures at baseline and at follow-up visits post-vaccination until day 28 post vaccination (reference ranges will be age appropriate)
- Number of participants with early discontinuation of vaccinations and reason for discontinuation until day 28 post vaccination

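### Table 4 grades heart rate and blood pressure with single, age-free cut-offs in participants from age 6, although the protocol makes laboratory ranges age appropriate, so vital-sign AE frequencies in the two paediatric cohorts may be distorted.

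*Protocol*

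**What the plan says.** **Scale and scope.** The Annex (Assessment of severity) opens: "The severity of clinical and laboratory AE will be assessed according to the scales in Tables 3 - 5". It makes no exception for age.

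**Heart rate.** The definitions under Table 4 describe tachycardia as "A disorder characterized by a dysrhythmia with a heart rate greater than 100 beats per minute" and set bradycardia at below 60 bpm. Grade 1 of either is "Asymptomatic, intervention not indicated". The footnotes ask for at least 10 minutes of rest. They call for clinical judgment only when characterising bradycardia.

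**Blood pressure.** Grade 1 hypertension is "Prehypertension (systolic BP 120 - 139 mm Hg or diastolic BP 80 - 89 mm Hg"). Grade 2 starts at 140/90 and grade 3 at 160/100 mm Hg. Hypotension, by contrast, is relative: "A disorder characterized by a blood pressure that is below the normal expected for an individual in a given environment".

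**Population and objective.** The Synopsis (Sample Size) lists "20 Volunteers aged between 6 and 12 years inclusive, who will receive" the same 2×10^7 pfu dose as 20 adolescents aged 13-17 and 62 adults. The primary objective in section 4.2 is "To evaluate the safety and tolerability of five different doses of VSVΔG-ZEBOV vaccine in three different age groups".

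**Age adjustment.** The laboratory bullet of the primary endpoints (section 4.3) adds "reference ranges will be age appropriate". Nothing comparable is said for vital signs.

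**Route to the data.** Vital signs are checked before and after injection at visit 2 (section 6.3) and at every follow-up visit (section 6.4). The Annex has unsolicited AEs of every severity entered in the CRF to day 28.

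**The concern.** Children and adolescents came in by amendment, and the protocol recognised for laboratory values that adult ranges do not carry over. The vital-sign scale was not given the same treatment. If resting heart rate is higher and blood pressure lower at age 6-12 than in adults (an assumption, since the protocol gives no norms), one scale errs in two directions: it over-records tachycardia and under-records hypertension in children.

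AE frequency and severity to day 28 are primary endpoints, and minors share a dose with cohort 3. Readers will set the age groups side by side, and a difference in either vital-sign term could then come from the cut-off and not from the vaccine.

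**Working it through.** **The plan's own figure.** The cohort sizes add up: 20 + 20 + 20 + 39 + 62 = 161 adults, and 161 + 20 + 20 = 201, as stated. The protocol gives no power calculation or expected AE rate to reproduce.

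**Number of readings.** The check after injection on day 0 and the visits on days 1, 2, 7, 14 and 28 make six post-vaccination readings within the AE window.

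**Chance that a single reading exceeds 100 bpm.** Assume normal resting rates: p = 1 − Φ((100 − mean)/SD).
- Mean 80, SD 10: 1 − Φ(2.00) = 2.3%.
- Mean 85, SD 12: 1 − Φ(1.25) = 10.6%.
- Mean 90, SD 12: 1 − Φ(0.83) = 20%.

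**Bounds for at least one of six.** The chance lies between p (readings fully correlated) and 1 − (1 − p)^6 (independent). For p = 10% this is 10% to 46.9%, or 2.0 to 9.4 of 20 children. For p = 2% it is 0.4 to 2.3 children, and for p = 20% it is 4.0 to 14.8.

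**Simulation between the bounds (six correlated normal readings, no vaccine effect).**

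| Quantity | Within-person correlation | Range over the assumptions | Mean 85, SD 12 |
|---|---|---|---|
| Children with any reading above 100 | 0.5 | 10-53% | 34% |
| Children with a new reading above 100 (not already above 100 before injection) | 0.5 | 8-35% | 25% |
| Same, new readings only | 0.8 | 5-20% | 14% |
| Adults (mean 68-72, SD 10), any reading | 0.5 | 0.4-1.3% | – |

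The second and third rows are the fairer ones, because an AE has to arise during or after administration. Together they give 5-35%, which is 1 to 7 of 20 children. For adults, about 1% of 62 is 0.6 of a participant.

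**Effect on group frequencies.** Take 20 children against 62 adults at the same dose, with Fisher's two-sided test at an assumed 0.05 and p = 10%. Each range runs from fully correlated to independent readings.
- *Tachycardia as its own term, adults assumed at 2%:* the test rejects from the artefact alone in 24% to 99.7% of trials.
- *Percentage with any AE:* with background rate b and artefact rate q, the child rate is 1 − (1 − b)(1 − q).
  - b = 30%: rises to 37-63%; rejection 7.5-70%, against 3.7% with no artefact.
  - b = 60%: rises to 64-79%; rejection 4.4-28%, against 3.6%.
  - b = 90%: rises to 91-95%; rejection 1.7-0.9%, against 2.2%.

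The single vital-sign term is sensitive. The any-AE percentage is hardly affected when most participants already report something.

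**Blood pressure.** No figure can be given without norms. The direction follows from the assumption: if normal pressure is lower in children, fixed bands starting at 120/80 leave some values that are high for age below grade 1.

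**A contradiction inside Table 4.** Grade 1 hypertension starts at 120/80, but the definition requires repeated elevation exceeding 140/90. A reading of 130/85 is grade 1 by the table and not hypertension by the definition, at any age.

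**The case against.** The strongest reply is that Table 4 grades the severity of an AE and does not create one. The Annex first requires the event to be untoward, the definition speaks of a disorder and a dysrhythmia, the rate is taken at rest, and section 6.5 leaves severity to the investigator's clinical consideration. Heart rate and blood pressure are not solicited events, and section 4.3 has no vital-sign endpoint. All of this stands. A reader might infer that ordinary child heart rates automatically become AEs, but the text does not say so. What remains is that each investigator must decide case by case whether, say, 105 bpm in a seven-year-old counts, with a scale that says it is gradable and a judgment note that covers bradycardia only.

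A reader might also infer that a primary child-versus-adult comparison is inflated. None is named. The Synopsis states the adult and paediatric aims in parallel, section 7 makes the primary analysis descriptive, and Fisher's test is set only across experimental groups in general.

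Nor do the blood pressure bands add to any inflation: under the stated assumption they lower child counts. Even there, a true rise is not always missed, because grade 2 includes a change criterion (a symptomatic diastolic increase of more than 20 mm Hg). Hypotension is already relative to the individual, so the scale is not uniformly adult.

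Finally, the size is wholly assumed. Headline figures such as 34% or 53% count children already above 100 before injection and treat every exceedance as a recorded AE. The model describes ages 6-12 and should not be applied to the 20 adolescents.

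**Conclusion.** The point holds in limited form. Table 4 fixes age-free limits for heart rate and hypertension and applies them to participants from age 6, while the protocol's only age adjustment concerns laboratory values. Applied as written, it can over-record tachycardia and under-record hypertension in the two paediatric cohorts, and so distort those frequencies beside adults at the same dose.

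The size is conditional. Under the assumptions shown, 5-35% of children aged 6-12 would have a new reading above 100 bpm without any vaccine effect, against about 1% of adults. How many become recorded AEs depends on investigator judgment. The effect on the percentage with any AE ranges from appreciable to almost none, depending on the background rate. The documents do not support a claim of bias in a primary comparison with adults. The point is still worth correcting, because investigators apply the annex at the visit and the grading is hard to undo consistently afterwards.

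**What to change.** 1. In Table 4 and its definitions, state that age-appropriate reference ranges for heart rate and blood pressure apply to participants aged 6-17, in line with the laboratory bullet of section 4.3. Name the source of the ranges. Write the rule by age and not by cohort number, since the Synopsis and section 5.3 number the child and adolescent cohorts the opposite way round.
2. Report vital-sign AEs as change from the participant's own pre-injection check at visit 2. If the SAP already does this, a cross-reference is enough.
3. Reconcile the grade 1 hypertension band (from 120/80) with the definition (exceeding 140/90), so that one starting point applies.

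The cost is one added column or note in the annex and a derivation from readings already taken. No new measurement or visit is needed. For minors already graded under the present table, the recorded values can be re-read against the age ranges.
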